#### Statistical analysis

Generalized estimating equations will be used to manage the correlated relationships between multiple implants in the same patient. The data of different patients are assumed to be independent. Each patient will be assigned a number, which will be an indicator (X) for primary and secondary outcome (Y). For the patient (i) and implants (j), mean model is logit(E(Yij|Xij)) = beta0 + beta1*I(Xij = 2) + beta2*I(Xij = 3), and variance model is Var(Yij|Xij) = E(Yij|Xij)*(1-E(Yij|Xij)). For patient-reported outcome (VAS), ANOVA will be used to assess the difference among the three groups. The level of significance is set at 0.05.

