### Allocation and blinding

The patients will be divided into three groups using randomization tables allocating the patient a number within a corresponding envelope: group 1: short implants (6 mm) alone; group 2: short implants (8 mm) combined with OSFE; group 3: standard implants (10 mm) combined with OSFE. The assignment will be concealed from the clinical operators until the beginning of implant surgery. The outcome examiners and patients will be kept blinded to the assignment.

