### Outcomes

#### Baseline assessment

Resonance frequency analysis (RFA) measurements, treatment time and patient-reported outcome will be recorded. RFA assessment will be performed immediately after surgery, 2 weeks later and 3 months after surgery. RFA measurements will be conducted by the Osstell™ mentor (Integration Diagnostics AB, Göteborg, Sweden). Treatment time will be calculated from incision beginning to suture finishing. Patients will be asked to give their answers regarding intraoperative discomfort and postoperative pain immediately and two weeks after surgery using a 100-mm visual analogue scale (VAS) with word descriptors "very dissatisfied" to "very satisfied" on the left and right respectively.

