#### Follow-up assessment

All the included patients will be recalled for clinical and radiographic assessment at 12, 24, 36, and 60 months after crown placement. Survival rates, complication rates and marginal bone level will be recorded. Implant survival rates are defined as the percentage of implants still retained in the mouth. Implant success is defined according to Cochran et al. 2002 [17]. Both biological and mechanical complications will be recorded. Periapical radiographs will be taken immediately after implant surgery, and at the 1-year, 3-year, and 5-year examination. For standardization, a paralleling technique with a Rinn film holder (XCP Instruments; Rinn Corporation, Elgin, IL, USA) will be conducted. Radiographic analysis will be conducted by a software program (SIDEXIS 1.12; Sirona Dental Systems GmbH, Bensheim, Germany). Biological complications refer to peri-implant mucositis (bleeding on probing positive, and without surrounding bone loss) and peri-implantitis (bleeding on probing positive, probe pocket depth ≥5 mm and with surrounding bone loss), and technical complications are veneer ceramic chipping, framework fracture, loss of retention, screw loosening, abutment and implant fracture.

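### The stated GEE describes its group covariate as the patient's number, and its logit/Bernoulli form is invalid for the continuous outcomes RFA, marginal bone level and treatment time

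*Protocol article*

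**What the plan says.** All of this is in the protocol article.

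- **Purpose of the GEE** (Statistical analysis): "Generalized estimating equations will be used to manage the correlated relationships between multiple implants in the same patient". Patients are taken as independent of one another, with i indexing patients and j implants.
- **Covariate** (same section): "Each patient will be assigned a number, which will be an indicator (X) for primary and secondary outcome (Y". Nowhere does the section say that X is the randomised group.
- **Mean** (same section): "mean model is logit(E(Yij|Xij)) = beta0 + beta1*I(Xij = 2) + beta2*I(Xij = 3".
- **Variance** (same section): "variance model is Var(Yij|Xij) = E(Yij|Xij)*(1-E(Yij|Xij".
- **The one exception** (same section): "For patient-reported outcome (VAS), ANOVA will be used to assess the difference among the three groups".
- **Allocation** (Allocation and blinding): "The patients will be divided into three groups using randomization tables allocating the patient a number within a corresponding envelope". Groups 1, 2 and 3 are listed directly after this.
- **Outcomes**: Objective and hypotheses lists survival, complications, RFA, marginal bone level, treatment time and VAS. Baseline assessment says "Treatment time will be calculated from incision beginning to suture finishing" and has RFA read by an instrument at three times. Follow-up assessment says "Survival rates, complication rates and marginal bone level will be recorded". The primary outcome, under Sample size, is implant survival.

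**The concern.** The section goes beyond naming a method. It writes out a covariate, a link and a variance function and says which outcomes they serve, and two parts of that statement do not fit the trial.

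The covariate is described as something each patient has individually, yet the formula treats it as having three levels. An analyst who followed the words would put the cluster identifier where the treatment belongs.

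The model is also declared for secondary as well as primary outcomes, but a logit mean with variance μ(1 − μ) describes a yes/no variable. Three listed outcomes are a stability reading, a length and a duration. If the stated model cannot serve them, another must be chosen later, possibly with the data in view. Treatment time matters in particular, because the Discussion names a shorter operation among the benefits hoped for from short implants.

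**Working it through.** The plan gives no figure on this point. The check compares the model with each outcome and adds a small simulated illustration.

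**Step 1. What X must be.** The linear predictor has an intercept and indicators for X = 2 and X = 3.

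- *X as patient number (1 to 150).* Each indicator equals 1 for one patient only. β1 and β2 contrast patient 2 and patient 3 with everyone else, and no group comparison is estimated.
- *X as group code (1, 2, 3).* Group 1 is the reference, and β1 and β2 are the log odds ratios of groups 2 and 3 against group 1.

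Only the second reading gives three levels, and it matches the three groups listed with the envelope number. The patient already enters as the cluster, through index i and the stated purpose of the GEE.

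**Step 2. Which outcomes the model suits.**

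| Outcome | Scale | Model stated | Suitable? |
|---|---|---|---|
| Implant survival (primary) | yes/no per implant | logit, μ(1 − μ) | yes |
| Success, complications | yes/no per implant | logit, μ(1 − μ) | yes |
| RFA | continuous | logit, μ(1 − μ) | no |
| Marginal bone level | continuous length | logit, μ(1 − μ) | no |
| Treatment time | continuous duration | logit, μ(1 − μ) | no |
| VAS | continuous | ANOVA | outside this point |

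**Step 3. Why it fails for the continuous outcomes.** logit(μ) = ln[μ/(1 − μ)] exists only for 0 < μ < 1, and μ(1 − μ) < 0 for every μ > 1. The documents give no means, so these are assumed values:

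- RFA, mean 70: 70 × (1 − 70) = −4830.
- Treatment time, mean 35 min: 35 × (1 − 35) = −1190.
- Bone level, mean 0.6 mm: 0.6 × 0.4 = 0.24, which is positive. The same length in tenths of a millimetre has mean 6, and 6 × (1 − 6) = −30. A model that works or fails according to the unit of length is not a model for a length.

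The sign does not depend on the exact value chosen; any mean above 1 gives a negative variance.

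**Step 4. Illustration.** One dataset was simulated: 150 patients, 50 per group, 1 to 3 implants each, binomial GEE with exchangeable correlation. Survival was set to the protocol's 85.7 % in group 1 and 92 % in groups 2 and 3. The continuous outcomes had the assumed means above, equal in all groups.

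- Survival, X = group: β1 = 0.54 (SE 0.45), β2 = 0.33 (SE 0.44), ordinary treatment log odds ratios.
- Survival, X = patient number: each indicator covered one patient, and both coefficients ran to about 24.4.
- RFA and treatment time, X = group: no convergence, all estimates undefined.
- Bone level, X = group: the software returned β1 = −0.06 and β2 = −0.43, but only because the simulated group means (0.63, 0.62 and 0.53 mm) lay between 0 and 1. A log odds ratio of a length in millimetres has no useful meaning.

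**The case against.** The strongest reply is that this is loose wording in a condensed article and that the primary analysis is intact. Much of that stands. With X as group, the model has the right form for implant survival: binary outcome, logit link, Bernoulli variance, clustering by patient. A reader might infer from the X sentence that the trial has no analysis that yields a treatment effect. The documents do not support this, because the three-level indicators and the allocation text both point to a group code.

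It can also be said that no section labels RFA, bone level or treatment time as secondary, that treatment time is recorded per operation and has no natural implant index, and that the formula was therefore perhaps meant only for binary implant-level outcomes. This is a fair guess at intent, but the text says otherwise. It extends Y to secondary outcomes, survival is the only outcome named as primary, and VAS is then singled out for a different method. The other listed outcomes are left under the GEE. The point therefore concerns the stated scope of a model, and goes beyond detail left to an analysis plan.

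Three further inferences are tempting and should not be drawn:

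- *The model cannot be fitted at all.* This is too absolute for bone level, where software may return numbers. The accurate word is invalid.
- *The lack of a visit term is an error.* Y carries no time index, which is consistent with analysis at one time point, and an analysis plan may supply visit handling.
- *A definite loss of efficiency follows.* A median split of a normal variable keeps 2/π, about 64 %, of the information, but nothing in the protocol proposes to dichotomise anything.

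**Conclusion.** The point holds in two parts of unequal weight.

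1. X is wrongly described as the patient's number. For implant survival this is a wording error. Read as the group code, the model estimates the intended contrasts.
2. The logit/Bernoulli model is stated for primary and secondary outcomes with VAS as the only exception. It is invalid for three of the six outcomes listed under Objective and hypotheses: RFA, marginal bone level and treatment time. No valid model is stated for these three.

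The size is best given as that count. No loss of power or bias can be put on it, because the documents give no standard deviations or effect sizes for these outcomes and no fallback analysis. The second part rests on taking the stated scope at its word and on the three measures being continuous, as the assessment sections describe them. It does not depend on how X is read or on the simulated values.

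**What to change.** Amend the Statistical analysis section, or the corresponding text of the analysis plan, before analysis:

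- Define X as the randomised group (1, 2 or 3; group 1 as reference) and the patient number as the GEE cluster identifier.
- Limit the logit/binomial GEE to implant survival, implant success and complications.
- For RFA and marginal bone level, state an identity-link (Gaussian) GEE or a linear mixed model with clustering by patient.
- For treatment time, one value per operation, state a patient-level linear model with group as the factor.

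The VAS analysis need not change for this purpose. Log scales and additional covariates are choices open to the trial team and are not part of this correction.

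The cost is analysis-plan wording and standard software. No new data are needed, and the form of the primary survival analysis is unchanged.

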#### Sample size

The primary outcome is the implant survival rate. The criterion for significance is set at α = 0.05 (type I error) and at β = 0.10 (type II error). The analysis is two-tailed. The survival rate reported by Esposito et al. 2014 (92 % in the longer group and 85.7 % in the short group) is used to estimate the sample size [15]. Forty-two cases per group can result in a power of 80 %. Assuming the dropout rate at 20 %, 50 cases per group and 150 cases in total are finally determined.

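### The stated secondary analyses contain the treatment arm and nothing else; naming pre-operative bone height and planned implant count as covariates would add precision at almost no cost (low severity).

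*Protocol article*

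**What the plan says.** **Models (Statistical analysis).** Generalized estimating equations (GEE) handle several implants in one patient. The equation is introduced as serving primary and secondary outcomes: "mean model is logit(E(Yij|Xij)) = beta0 + beta1*I(Xij = 2) + beta2*I(Xij = 3"). Its variance is binomial. For VAS, "ANOVA will be used to assess the difference among the three groups". No covariate appears in either.

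**Allocation (Allocation and blinding).** Randomisation tables and envelopes are used, with no stratification factor named.

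**Information available.**
- Initial bone height is assessed on radiographs before surgery (Overview), and entry is limited to a residual bone height of 6 to 8 mm (Inclusion criteria).
- Treatment time is defined per operation: "Treatment time will be calculated from incision beginning to suture finishing" (Baseline assessment).
- At follow-up, "Survival rates, complication rates and marginal bone level will be recorded" (Follow-up assessment). Periapical films are taken immediately after surgery and at 1, 3 and 5 years.
- The number of implants per patient is implied by the implant index in the model but is not listed as a recorded variable.

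**The concern.** An arm-only analysis leaves all variation due to baseline differences in the error term, and nothing in the stated design balances those differences.

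The case is clearest for treatment time and VAS. Treatment time has one value per operation, and VAS belongs to the patient. Both plausibly depend on how many implants the session involves. Clustering by GEE deals with correlation between implants; it does nothing for an outcome that exists once per session or per patient. These two outcomes also carry the benefit the article hopes to show for short implants: less operating time and less postoperative discomfort (Discussion).

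For resonance frequency analysis (RFA) and marginal bone level, residual bone height is the obvious pre-operative covariate. For bone level the article also leaves open how the first film is used. A bare level at 1, 3 or 5 years would mix bone loss with how deep the implant was set.

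**Working it through.** **1. The plan's own figure.** No stated number bears on covariate adjustment. The only sizing figure concerns implant survival: rates of "92 % in the longer group and 85.7 % in the short group", "The criterion for significance is set at α = 0.05 (type I error) and at β = 0.10 (type II error"), "The analysis is two-tailed", and "Forty-two cases per group can result in a power of 80" %. It does not reproduce. With a two-sided α of 0.05 and pooled variance under the null, 80 % power needs

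(1.960·√(2·0.8885·0.1115) + 0.842·√(0.92·0.08 + 0.857·0.143))² / 0.063² ≈ 391 per arm,

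and 42 per arm gives 14.7 %. That is a separate problem. Only the planned 50 per arm is used below. The Overview instead states 225 patients, or 75 per arm if equal, so that value is shown where it matters.

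**2. Gain from a covariate.** With correlation r between covariate and outcome, residual variance is multiplied by 1 − r². With 50 per arm, the standardised difference that has 80 % power unadjusted is (1.960 + 0.842)·√(2/50) = 0.56 SD. Adjusted power for that difference is Φ(2.802/√(1 − r²) − 1.960). The documents give no r, so a range is assumed.

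| Assumed r | Variance removed (r²) | Power for 0.56 SD | Patients per arm giving the same precision, 50·(1 − r²) |
|---|---|---|---|
| 0.1 | 1 % | 80.4 % | 49.5 |
| 0.2 | 4 % | 81.6 % | 48.0 |
| 0.3 | 9 % | 83.6 % | 45.5 |
| 0.5 | 25 % | 89.9 % | 37.5 |

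**3. Chance imbalance.** The standard error of the difference in covariate means between two arms is √(2/n) SD, or 0.20 SD at n = 50. A given pair of arms differs by more than 0.3 SD with probability 13 % at 50 per arm, 18 % at 40 and 7 % at 75.

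- *Bone height.* If it is uniform over 6 to 8 mm (assumption), its SD is 2/√12 = 0.58 mm. The 95 % range of a chance difference between two arms of 50 is ±1.96·0.58·0.20 = ±0.23 mm. The narrow entry range limits what this covariate can explain.
- *Implant count.* Suppose 30 % of patients have two implants and the second adds 15 to 20 minutes (both assumptions). The standard error of the difference in that share is √(2·0.3·0.7/50) = 0.092. A 10-point imbalance is thus about one standard error, and a larger one occurs in about 28 % of trials for a given pair. Ten points shift the mean difference in treatment time by 0.10·15 to 0.10·20 = 1.5 to 2.0 minutes.

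**4. Use of the first film.** Take equal SDs at both films (assumption), with variances relative to the follow-up level alone.

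| Assumed r between films | Simple change, 2(1 − r) | Adjusted for first film, 1 − r² |
|---|---|---|
| 0.3 | 1.40 | 0.91 |
| 0.5 | 1.00 | 0.75 |
| 0.7 | 0.60 | 0.51 |

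Simple change is noisier than the bare level when r is below 0.5. Its justification is that it measures bone loss, not that it is always more precise.

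**The case against.** Four objections carry weight.

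- **The equation is for binary outcomes.** A logit link with binomial variance fits survival, success and complications. It cannot describe bone level, RFA or treatment time, so it cannot show that those outcomes will be analysed in a particular unadjusted way. This stands. But the article presents the equation as covering secondary outcomes and names ANOVA for VAS outright. A model for the continuous outcomes has to be written anyway, and covariates can be named then.
- **Covariates are often left to an analysis plan, and none is shown.** This stands where the article is silent. It has less force for VAS, where the method is fixed.
- **Unadjusted comparisons are valid.** This stands. The unadjusted standard error already allows for chance imbalance, and the 10-point example above is ordinary sampling variation.
- **Some candidate covariates arise after allocation.** The first film and the number of implants actually placed both follow randomisation. This stands and shapes the fix.

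A reader might infer that bone height, first film and implant count are all collected and then ignored. The documents do not support that. Multiple implants enter the GEE as clusters, implant count is not listed as recorded, and nothing says bone level will be analysed without reference to the first film.

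**Conclusion.** The secondary analyses, as far as they are stated, use no baseline information. The point is firmest for VAS, where plain ANOVA is specified, and for treatment time, which has one value per operation. It is weaker for RFA and marginal bone level, where no suitable model is given and the bone-height range is narrow.

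The cost is efficiency on secondary outcomes: about 4 to 25 % of residual variance if r is 0.2 to 0.5, and next to nothing at 0.1. These correlations are assumptions, as are the share of two-implant patients and the minutes per extra implant, so the true size cannot be computed from the documents. A claim that arm effects will be biased would go too far, because allocation is random. Severity is low; this is a free improvement.

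**What to change.** Amend the Statistical analysis section as follows.

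- **VAS and treatment time:** patient-level ANCOVA with arm and the number of implants planned before the envelope is opened. Record that planned number. Do not substitute the number placed, which is determined after allocation.
- **RFA and marginal bone level:** linear models (Gaussian GEE, to keep the clustering of implants within patients) with arm and pre-operative residual bone height as a continuous covariate.
- **Bone change:** define it relative to the immediate post-surgical film. That film is taken after allocation and surgery, and the procedure may affect it, so its first role is as reference. If it is also entered as a covariate, state that caveat.
- **Immediate RFA:** do not use it as a covariate, because treatment can affect it.
- **Implant survival:** leave the primary model unadjusted. At the assumed rates and one implant per patient, 50 per arm gives only about 50·0.08 = 4 to 50·0.143 = 7 implant losses per arm.

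The cost is a few sentences, a note of the planned implant number, and one or two extra terms in the secondary models. Bone height and the films are already scheduled. Fixing the covariates before outcome data are seen also removes any later choice among them.

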#### Missing data

Sample size calculation was performed accounting for possible loss to follow-up. Moreover, we will account for the data not missing at random due to unbalanced loss to follow-up by handling drop-outs as nonsuccess or nonsurvival using the intention-to-treat principle.

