## Method/Design

### Overview

The proposed study is designed as a prospective single-center, three-arm parallel group, randomized controlled trial. We plan to enroll 225 patients in need of dental implant treatment in the posterior maxilla. The study (Number [2015]16) has been approved by the Ethics Committee of Shanghai Ninth People’s Hospital, China. In addition, the study has been registered in ClinicalTrials.gov and the identifier number is NCT02350075. The clinical component of the study will be initiated in September 2015 at the Department of Oral and Maxillofacial Implantology, Shanghai Ninth People’s Hospital, Shanghai Jiao Tong University, China.

The systematic health condition of all the participants will be recorded and they should fulfill the following criteria. Before the implant surgery, all patients will receive clinical and radiographic assessment. All patients will be required to receive oral hygiene instructions before implant surgery. Panoramic and periapical radiographs will be taken to assess the initial bone height and width. If necessary, cone-beam computed tomography will be performed.

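### The drop-out rule reaches only survival and success; marginal bone level has no rule for losses, and the stated GEE neither fits it nor uses the earlier films of patients who leave

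*Protocol article*

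**What the plan says.** All references are to the protocol article.

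- **Follow-up assessment** recalls patients "at 12, 24, 36, and 60 months after crown placement" and states: "Survival rates, complication rates and marginal bone level will be recorded". Periapical films are scheduled right after surgery and at the 1-, 3- and 5-year examinations.
- **Missing data** makes an unrestricted promise: "we will account for the data not missing at random due to unbalanced loss to follow-up". The device for keeping it is "handling drop-outs as nonsuccess or nonsurvival using the intention-to-treat principle". No other outcome is named.
- **Statistical analysis** applies one GEE to the primary and secondary outcomes: "For the patient (i) and implants (j), mean model is logit(E(Yij|Xij)) = beta0 + beta1*I(Xij = 2) + beta2*I(Xij = 3"). The variance is the mean times one minus the mean. The indices are patient and implant, the only covariate is group, and there is no visit. The pain and discomfort scales get a separate ANOVA; bone level gets no separate method.
- **Sample size** names implant survival as primary and says: "Assuming the dropout rate at 20 %, 50 cases per group and 150 cases in total are finally determined".

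**The concern.** The plan names a specific threat, loss that differs between arms and depends on outcome, and says that it will deal with it. The device works by assigning a bad category, so it works only where there is a category to assign. Marginal bone level is a measurement in millimetres, and calling a patient a nonsurvival or a nonsuccess gives it no value.

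The stated model does not fill the gap. It is a model for a yes/no response with one value per implant. An analyst who follows the text has no usable model for bone level and no instruction on how a patient filmed at years 1 and 3, but not at year 5, should count.

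At stake is one of the main 5-year comparisons of 6-mm implants with longer implants plus OSFE. If patients with early bone loss leave one arm more often, that arm can look better at year 5, although the films that would show the problem were taken.

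**Working it through.** **1. The plan's own loss figure.** Sample size gives 20 % drop-out and 50 per group. 50 × 0.20 = 10 patients per group, and 150 × 0.20 = 30 in total. The Overview gives a different total ("We plan to enroll 225 patients in need of dental implant treatment in the posterior maxilla"), on which 225 × 0.20 = 45. That conflict is a separate matter; the share lost is the same.

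**2. What the rule can score.**

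| Follow-up outcome | Type | Value for a drop-out under the rule |
|---|---|---|
| Survival | binary | nonsurvival |
| Success | binary | nonsuccess |
| Marginal bone level | continuous, mm | none |
| Complications | yes/no or rate | none stated |

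**3. What the GEE can analyse.** A logit mean requires E(Y) between 0 and 1, and variance E(Y)(1 - E(Y)) is that of a binary Y. Bone level in mm meets neither condition. The article gives no cut-off that would turn it into a binary outcome. With indices i (patient) and j (implant) only, there is one Y per implant and no term to separate years 1, 3 and 5.

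**4. How large the effect could be.** The documents give no bone-level SD, no correlation between visits and no split of the 20 % by arm or visit. The following are therefore assumptions:

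- two arms of 50, one implant each, no true arm difference;
- mean bone loss 1.0, 1.1 and 1.2 mm at years 1, 3 and 5, SD 0.8 mm, correlation between visits 0.6 to 0.8;
- loss of 10 % in one arm, unrelated to outcome, and 30 % in the other, related to bone loss (logistic, slope 1.2 per SD), so (10 + 30)/2 = 20 % on average;
- every leaver has a 1-year film.

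The difference is the heavier-loss arm minus the other at year 5, so a negative value makes the heavier-loss arm look better. "Available films" means patients with a 5-year film; "likelihood" means an analysis that also uses the earlier film.

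| What the 30 % loss depends on | Available films | Likelihood, earlier film used |
|---|---|---|
| 1-year bone loss (observed) | -0.14 to -0.18 mm | about 0 |
| 5-year bone loss (unobserved) | about -0.23 mm | -0.16 to -0.09 mm |

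In the first row the standard error of the available-film difference is about 0.17 to 0.19 mm, so the bias is roughly 0.8 to 1.0 standard errors (0.139/0.179 = 0.78 at correlation 0.6; 0.181/0.174 = 1.04 at 0.8).

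In the second row the likelihood analysis keeps 0.09/0.23 = 39 % to 0.16/0.23 = 70 % of the bias.

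**5. Milder cases.** With loss depending on 1-year bone loss in the same way in both arms, 15 % versus 25 % gives an available-film bias of about -0.05 mm (0.3 standard errors), and 20 % versus 20 % gives about 0. With loss unrelated to outcome the bias is 0.

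**The case against.** **It belongs in the SAP.** Missing-data handling for secondary outcomes is usually SAP content, the SAP is not shown, and the primary outcome is covered by the rule. This stands as a limit on importance: only a secondary outcome is affected, and silence alone would be no finding. But the article is not silent. It claims to account for not-at-random loss, names a device that cannot do so for bone level, and writes out one equation for primary and secondary outcomes that does not fit it.

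**A reader might infer that the GEE compares bone level among stayers only, or that earlier films are thrown away.** The documents support neither. The GEE as written cannot compare millimetres in anyone, and nothing restricts bone level to 5-year completers or discards data collected before a patient leaves. The available-film figures above show what a simple 5-year comparison would risk, not what the plan commits to.

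**A reader might likewise infer that complications recorded before drop-out are lost, or that unobserved years count as complication-free.** The text says neither. It leaves the counting open, which is a minor clarification. Counting over observed implant-years would itself assume uninformative censoring.

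**The mixed model does not meet the stated threat.** Its near-zero bias arises when loss is explained by the observed 1-year film, which is missing at random, whereas the plan fears loss not at random. This stands. Under that mechanism the model only reduces the bias, so a sensitivity analysis has to accompany it.

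**The scenario is harsh.** Loss of 10 % versus 30 %, outcome-related in one arm only, is an assumption. This also stands; step 5 shows how quickly the bias shrinks.

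**Conclusion.** The point holds in a limited form. From the text alone, the promise to account for not-at-random loss is kept, at most, for survival and success. Marginal bone level has no drop-out rule, no model that suits its scale and no stated way to use the earlier films of patients who leave.

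The possible bias ranges from nil to about -0.23 mm under the assumptions shown, and its direction depends on which arm loses more patients and why. None of this can be derived from the documents, which give only an overall 20 %. The primary outcome is untouched by this point. It should be corrected because the correction is cheap and the stated method cannot be carried out for this outcome, not because a given bias has been shown.

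**What to change.** - In **Missing data**, limit the nonsuccess/nonsurvival rule to those two outcomes and say so.
- In **Statistical analysis**, keep the logit GEE for binary outcomes. For marginal bone level, use a linear mixed model on all scheduled films with arm, visit and arm-by-visit terms and random effects for patient and implant. Leavers then contribute the films they have, and implants in one patient stay correlated.
- Add one sensitivity analysis that shifts the unobserved bone levels of drop-outs by a fixed amount, varied by arm, and report how large a shift would change the conclusion. This is the part that addresses the not-at-random concern.
- As a minor clarification, state how complications recorded before drop-out, and the time after it, are counted.

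Cost: wording and a little more programming; no new patients, visits or films. Downside: the main model assumes that drop-out is explained by earlier films, which the shift analysis probes but cannot verify.
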